## 3.6 Data collection

An adapted WHO stepwise questionnaire will be used to collect information on demographic characteristics (age, sex, occupation), history of hypertension, other CVD risk factors, and health behaviours (smoking, alcohol drinking, diet, and physical activity) of participants at baseline and follow-up visits. The international physical activity questionnaire (IPAQ)(Craig et al., 2003) will be used to collect data on physical activity. The tools will be translated and validated in the local context. We will collect detailed data on patients care cascade during the home visits and monitor their ability to control their BP with the combination of medical management and the CHW intervention. Three BP measurements, body weight, height and waist circumference will be obtained at each data collection visit by outcome assessors masked to intervention assignment.

The primary outcomes will be the differences in systolic and diastolic BP changes from baseline to the end line survey. Secondary outcomes will include the proportion of patients with controlled hypertension (BP <140/90 mm Hg) ) according to the Kenyan national guidelines(Division of Non-Communicable Diseases-Ministry of Health, 2018), body composition – Body mass index(BMI), waist circumference . Low physical activity will be defined as less than 150 minutes of moderate physical activity or 75 minutes of vigorous activity each week. To assess the outcome of the intervention the survey conducted at baseline will be conducted at 3 months of follow-up and at the end of 6 months of intervention.

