## 2.2 Broad Objectives:

To determine the feasibility and preliminary efficacy of a homebased intervention for the control and management of hypertension amidst the COVID-19 Pandemic in Kiambu County, Kenya

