## 3.4 Sample size and power calculation

With changes in BP as the primary outcome we calculated a sample of 52 between the 2 groups to show changes in BP between the intervention and control groups at a significance level of 0.05 for a two-sided test with 80% statistical power of finding a large effect (*Cohen’s d*=0.80). This study will be underpowered to find significantly small effect (*Cohen’s d*=0.30) and moderate effect (*Cohen’s d*=0.50), however, we will be able to calculate an effect size and the direction of its impact.

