## 3.9 Data analysis

We will use STATA version 15 software for statistical analyses. The differences between the control and intervention groups on baseline demographics, biological and behavioral measures will be assessed using nonparametric (chi square test) and parametric tests(t-test) as appropriate. Generalized estimating equations (GEE) approach of Zegar and Liang(Zeger & Liang, 1986) will be used to analyze how BP vary over the six months after adjusting for intervention group, baseline characteristics and healthy diet while adjusting for demographic characteristics. For the secondary outcome variables, we will use GEE analysis for changes in BMI and mixed model analysis of changes in WHtR after adjusting for the interventions ,baseline characteritics and use of antihypertensives. The GEE model will be used to examine the association between the CHW intervention with BP control and normal BMI, reporting odds ratios, after controlling for baseline measurements and use of antihypertensive medication. Statistical significance will be considered at P < 0.05.

##

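### Section 3.6 names two primary outcomes but section 3.4 sizes the trial for one, and with no rule for combining them the stated 5% error and 80% power cannot both hold

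*Protocol*

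**What the plan says.** Three sections of the protocol bear on this.

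- **Section 3.6 (Data collection)** has two primary outcomes, unordered: "The primary outcomes will be the differences in systolic and diastolic BP changes from baseline to the end line survey".
- **Section 3.4 (Sample size and power calculation)** has one, and does not say whether it is systolic or diastolic: "With changes in BP as the primary outcome we calculated a sample of 52 between the 2 groups". The design values are those of one test: "at a significance level of 0.05 for a two-sided test with 80% statistical power", for a standardised difference of 0.80.
- **Section 3.9 (Data analysis)** sets one threshold for everything: "Statistical significance will be considered at P < 0.05". Its GEE model is described for BP as a whole ("will be used to analyze how BP vary over the six months after adjusting for intervention group, baseline characteristics and healthy diet"), without ranking systolic against diastolic.

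No section states an order of testing, a split of the significance level, or whether success means either outcome or both. Section 2.2 gives the broad aim: "To determine the feasibility and preliminary efficacy of a homebased intervention for the control and management of hypertension".

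**The concern.** The error rate and power in section 3.4 belong to one hypothesis test, whereas section 3.6 makes the primary question two tests. What happens to those two figures depends on a decision rule that the protocol does not give. A rule that accepts either outcome raises the chance of a false positive above 5%. A rule that requires both lowers the power below 80%.

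At stake is how the main result can be read. If one component reaches P < 0.05 and the other does not, the protocol gives no basis for saying whether the primary objective was met. The results are also meant to inform a later fully powered trial (section 1.2), so an ambiguous primary result would carry forward into that planning.

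**Working it through.** **Inputs from the protocol.** Two primary outcomes (3.6). N = 52 in total, two-sided alpha 0.05, power 80%, d = 0.80 (3.4). Threshold P < 0.05 (3.9).

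**Assumed, because the protocol does not give them.** 1:1 allocation, so 26 per arm. A correlation r between systolic and diastolic change, shown over a range. Unadjusted two-sample t-tests in place of the adjusted GEE.

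**Step 1: reproduce the stated N.** For n per arm, the noncentrality is d × √(n/2), with 2n − 2 degrees of freedom. With n = 26 this is 0.80 × √13 = 2.88 on 50 df, and the exact power is 80.7%. With n = 25 it is 79.1%. So 26 per arm, 52 in total, is the smallest size reaching 80%. The stated N is correct for one outcome tested at 0.05.

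**Step 2: either outcome counts as success.** The familywise error is 1 − P(|Z1| < 1.96 and |Z2| < 1.96), where Z1 and Z2 have correlation r. If the outcomes are independent it is 1 − 0.95² = 1 − 0.9025 = 9.75%, which is the maximum.

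| r (assumed) | Familywise error |
|---|---|
| 0 | 9.75% |
| 0.5 | 9.1% |
| 0.6 | 8.75% |
| 0.7 | 8.35% |
| 0.75 | 8.1% |
| 0.8 | 7.8% |
| 0.9 | 7.0% |

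The value tends to 5% only as r tends to 1. Simulated pairs of t-tests with 26 per arm agree to within about 0.1 percentage point.

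**Step 3: both outcomes are required.** The error cannot exceed 5%. With a true d of 0.80 on each outcome and independence, joint power is 0.807² = 65%. By simulation it is about 70% at r = 0.5, 71% at 0.6, 72% at 0.7, 74% at 0.8 and 76% at 0.9. It approaches the single-test 80.7% only as r tends to 1.

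**Step 4: split the significance level, 0.025 each.** The familywise error is at most 1 − 0.975² = 4.9%. Power per outcome with 26 per arm falls from 80.7% to 71.6%. Reaching 80% needs 31 per arm (80.0%; 30 per arm gives 78.5%), which is 62 in total.

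**Step 5: one primary outcome, the other tested only if the first succeeds.** The first test is at 0.05, so the error is held at 5%. Power for the first outcome is the 80.7% of step 1, and N stays at 52.

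**The case against.** Four arguments weigh against the point.

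**No success rule is stated.** A reader might infer that the protocol lets a significant result on either component count, so that the trial's false-positive rate simply is 8-9%. The text does not support that. Sections 3.6 and 3.9 list outcomes and a threshold but say nothing on how the outcomes combine, and no correlation is given. If both are required, the error does not exceed 5%. Nor does anything allow only the favourable component to be reported, since both are prespecified. This objection stands: the percentages must be given as conditional.

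**The rule could sit in an SAP.** That is fair for the combination rule alone. It does not cover the mismatch inside the protocol, where 3.4 sizes for one primary outcome and 3.6 declares two. An SAP rule accepting either or requiring both would still leave 3.4 describing the error rate and power of a single test.

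**This is a pilot.** The broad aim is feasibility and preliminary efficacy, and section 3.4 admits low power for small and moderate effects and values the effect estimate and its direction. This lowers the weight. It does not remove the point, because specific objective iii (section 2.3) is to determine effectiveness, and the protocol sets out a formal powered test and a significance rule.

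**The calculation is not the planned analysis.** The figures come from unadjusted t-tests, while section 3.9 plans an adjusted GEE, and 1:1 allocation is assumed. The percentages are therefore illustrative. The same simplification does reproduce the protocol's own 52.

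**Conclusion.** The point holds in conditional form. The protocol conflicts with itself on whether there is one primary outcome or two, and its 5% error and 80% power hold together only for one.

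- If either outcome suffices, the familywise error is above 5% for any correlation below 1 and at most 9.75%. The 8-9% range applies only if the two changes correlate at about 0.5-0.75.
- If both are required, error is controlled, but power is about 70-74% at correlations of 0.5-0.8 (about 65% if independent), given d = 0.80 on each outcome.

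The importance is moderate: the trial is a preliminary-efficacy study, but the correction is cheap and removes a real ambiguity about what its primary result would be.

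**What to change.** In section 3.6, name one BP measure at 6 months, for example the change in systolic BP, as the single primary outcome tested at two-sided 0.05. Make the other measure the first secondary outcome, tested at 0.05 only if the first is significant. In section 3.4, state that the calculation with d = 0.80 refers to the named measure.

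This takes about one sentence in each section, and N stays at 52. The small downside is that the second measure can no longer carry the primary claim alone.

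If both are kept as primary, state the decision rule and restate the power. It is about 72% per outcome at 0.025 each (62 patients would be needed for 80%). If both must be significant, it is about 70-74% under the assumed correlation of 0.5-0.8.

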|  | **Physical activity ( IPAQ)**  The questions will ask you about the time you spent being physically active in the last 7 days. Please answer each question even if you do not consider yourself to be an active person. Please think about the activities you do at work, as part of your house and yard work, to get from place to place, and in your spare time for recreation, exercise or sport. | |
|  | Think about all the vigorous activities that you did in the last 7 days. Vigorous physical activities refer to activities that take hard physical effort and make you breathe much harder than normal. Think only about those physical activities that you did for at for atleast 10 minutes at a time.  During the last 7 days, on how many days did you do vigorous physical activities like heavy lifting, digging, aerobics, or fast bicycling? | 1. -------------- days per week 2. No vigorous activity (**Skip to number 3)** |
|  | How much time did you usually spend doing vigorous physical activities on one  of those days? | 1. ………… hours per day  2. ………… minutes per day  Don’t know/Not sure |
|  | Think about all the moderate activities that you did in the last 7 days. Moderate activities refer to activities that take moderate physical effort and make you breathe somewhat harder than normal. Think only about those physical activities that you did for at least 10 minutes at a time.  During the last 7 days, on how many days did you do moderate physical activities like carrying light loads, bicycling at a regular pace, or doubles tennis?  Do not include walking. | 1.--------------------days per week  2. No moderate physical activities **(Skip to question 5)** |
|  | How much time did you usually spend doing moderate physical activities on one  of those days? | 1……………hours per day  2……………. minutes per day  3.Don’t know/Not sure |
|  | Think about the time you spent walking in the last 7 days. This includes at work and at home, walking to travel from place to place, and any other walking that you have done solely for recreation, sport, exercise, or leisure.  During the last 7 days, on how many days did you walk for at least 10 minutes  at a time? | 1.……………. days per week  2.No walking Skip to question 7 |

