|  | *The last question is about the time you spent sitting on weekdays during the last 7 days. Include time spent at work, at home, while doing course work and during leisure time. This may include time spent sitting at a desk, visiting friends, reading, or sitting or lying down to watch television*.  During the last 7 days, how much time did you spend sitting on a week day? | 1.…………… hours per day  2……………. minutes per day  Don’t know/Not sure |
| **History of Raised Blood Pressure** | | |
|  | Have you ever had your blood pressure measured? |  |
|  | Have you ever been told by a doctor or other health worker that you have raised blood pressure or hypertension? |  |
|  | Are you on any treatments/advice for high blood pressure? | |
|  | Drugs (medication) that you have taken in the past two weeks |  |
|  | Advice to reduce salt intake |  |
|  | Advice or treatment to stop smoking |  |
|  | Advice to start or do more exercise |  |
| **Step 2 Physical Measurements** | | |
|  | Interviewer ID |  |
|  | Device IDs for height and weight |  |
|  | Height(cm) |  |
|  | Weight(kg) |  |
|  | **For women:** Are you pregnant? |  |
|  | Waist circumference(cm) |  |

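### As printed, the survey collects no walking time and the low-activity rule ignores walking, so people active mainly by walking are classed as low; the rule also misclassifies mixed moderate and vigorous activity

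*Protocol*

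**What the plan says.** Protocol section 3.6 names the IPAQ as the tool that "will be used to collect data on physical activity" and then fixes the classification: "Low physical activity will be defined as less than 150 minutes of moderate physical activity or 75 minutes of vigorous activity each week". Walking is not mentioned in that sentence.

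Appendix 2 prints the activity items:

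- Vigorous activity has a days item and a time item ("How much time did you usually spend doing vigorous physical activities on one" of those days).
- Moderate activity has the same pair ("How much time did you usually spend doing moderate physical activities on one" of those days), and its days item carries the instruction "Do not include walking".
- Walking has a days item only. Its negative answer reads "No walking Skip to question 7", and the next printed item is weekday sitting time.

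On a separate detail of the same form, section 3.6 says "Three BP measurements, body weight, height and waist circumference will be obtained at each data collection visit". Step 2 of Appendix 2 has rows for the interviewer, "Device IDs for height and weight", height, weight, pregnancy and waist, but no row for blood pressure.

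**The concern.** The definition and the form do not fit together. The form takes walking out of the moderate category and does not measure its duration; the definition then counts only moderate and vigorous minutes. Walking therefore contributes nothing, however much of it a participant does. A physical activity programme with set targets is a named part of the intervention (section 3.8), so the activity measure should be able to register an ordinary way of becoming more active.

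The loss cannot be repaired at analysis. An analysis plan can change a scoring rule, but it cannot supply minutes that were never asked for.

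The threshold sentence has a second weakness. It joins two cut-offs with 'or' and gives no rule for combining them, so people who do some of each kind of activity are judged on each part separately.

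**Working it through.** The plan gives no figure to reproduce here. The check sets the form against the definition and then applies the definition to example weeks. The minutes in the examples are illustrative assumptions, not figures from the protocol.

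**1. Is the walking-time item absent?** The skips in Appendix 2 reveal the intended numbering:

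- No vigorous activity skips to item 3, passing vigorous time (item 2).
- No moderate activity skips to item 5, passing moderate time (item 4).
- No walking skips to item 7, which should pass an item 6.

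The printed sequence is vigorous days (1), vigorous time (2), moderate days (3), moderate time (4), walking days (5), then sitting (7). Item 6 is missing, and by the pattern of the other pairs it would be walking time.

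**2. Can weekly walking minutes be derived from days?** The item counts days with at least 10 minutes of walking at a time, so *k* days give only a lower bound of 10*k* minutes. Reaching 150 needs 150/*k* minutes a day, which the form does not record.

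| Walking days | Minimum implied (min/week) | Needed per day to reach 150 (min) |
|---|---|---|
| 3 | 30 | 50 |
| 5 | 50 | 30 |
| 7 | 70 | 21.4 |

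**3. How does the definition classify example weeks?** Let W, M and V be weekly walking, moderate and vigorous minutes.

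- Reading A: low if M < 150 and V < 75 (neither threshold met).
- Reading B: low if M < 150 or V < 75 (literal 'or').
- Combined without walking: low if M + 2V < 150. The weight is 150/75 = 2.
- Combined with walking: low if W + M + 2V < 150.

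| W, M, V | Reading A | Reading B | M + 2V | W + M + 2V |
|---|---|---|---|---|
| 150 (5 × 30), 0, 0 | low | low | 0, low | 150, not low |
| 420 (7 × 60), 0, 0 | low | low | 0, low | 420, not low |
| 150, 60, 0 | low | low | 60, low | 210, not low |
| 0, 100, 50 | low | low | 200, not low | 200, not low |
| 0, 300, 0 | not low | low | 300, not low | 300, not low |
| 154 (7 × 22, slow), 0, 0 | low | low | 0, low | 154, not low |

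The first three rows show the walking problem under either reading. The fourth shows that the mixed-activity problem also arises under either reading. The fifth is a problem only under the literal reading. The last shows the price of counting all walking as moderate.

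**4. Where can the classification reach results?** Section 3.6 lists the secondary outcomes as blood pressure control, BMI and waist circumference. Section 3.9 models blood pressure, BMI, waist-to-height ratio, blood pressure control and normal BMI. Low activity is in neither list. It can enter through baseline cardiometabolic risk (section 2.3, objective ii), through the comparison of arms on behavioural measures at baseline, and as a covariate if it is counted among the baseline characteristics (section 3.9).

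**The case against.** **The missing item may be a lost row.** The skip to item 7 fits a row dropped in document conversion as well as an author's omission, and section 3.6 says the tools are still to be translated and locally validated. This stands as a caution: the source form must be checked first. It does not rescue the definition, which ignores walking even if the time item exists.

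**The stakes could be overread.** A reader might infer that the trial could wrongly conclude the programme did not change activity. The protocol does not support that: it specifies no between-arm test of change in activity. Activity in the intervention arm is also followed through adherence to the personal programme (section 3.7), review of targets at home visits, and a smart watch (section 3.8). This limits the consequence, although nothing ties the watch to the low-activity definition.

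**The blood pressure row could be overread too.** A reader might infer from Step 2 that the primary outcome goes unrecorded. That does not follow. Sections 3.6 and 3.8 require the measurements, a protocol need not reproduce every recording form, and section 3.5 already uses a separate paper register at screening.

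**The 'or' wording has a natural reading**, that low means neither threshold is met, and scoring detail is often left to the analysis plan. That disposes of the 300-minute example, but not of the 100 + 50 example, which is classed as low under both readings of a rule that the protocol itself fixes.

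**Counting all walking as moderate is a choice.** The item covers walking for travel and at work and does not ask about pace, so slow walkers would cross the threshold. This is correct, and it is why both versions should be reported.

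**Conclusion.** The point holds with limited scope. On the form as printed, a participant whose only activity is walking is classed as low whatever the amount, 150 or 420 minutes a week alike, and the minutes cannot be reconstructed. Separately, mixed activity worth 200 moderate-equivalent minutes is classed as low because neither threshold is met on its own.

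This rests on three assumptions: that the walking-time item is truly absent from the source form, that moderate activity is scored from the form's moderate item, and that 150 and 75 imply a weight of 2. The walking misclassification applies only to people who do not otherwise reach the thresholds; the protocol gives no basis for estimating how many that would be.

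The effect is on descriptive and behavioural activity results: baseline risk, arm comparisons and possibly covariates. It does not touch the primary blood pressure outcome or any modelled secondary outcome. The absent blood pressure row is a minor form check and no evidence that readings are lost.

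**What to change.** 1. Check Appendix 2 against the source form. If the item is absent there, restore a question on usual walking time per day (hours and minutes) immediately before the sitting item, and use the same form at baseline, 3 months and 6 months.
2. Replace the threshold sentence in section 3.6 with one combined rule: low physical activity is walking + moderate + 2 × vigorous minutes below 150 per week.
3. State the downside, that pace is not recorded and slow walking counts as moderate, and report the classification both with and without walking.
4. As a form check only, confirm that the three blood pressure readings have a recording field at each assessment visit.

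The cost is one question per assessment, one rewritten sentence and one extra line in the activity table. It should be done before the first baseline assessment, because walking time for any visit already completed cannot be recovered from the form.

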## 3.7 Data for feasibility and acceptability assessment

At the end of the study, participants in the intervention arm will complete the Client Satisfaction Questionnaire(Larsen et al., 1979) to assess acceptability of the CHW intervention. In addition, 10 patients (purposively sampled to include both gender and different age groups) and CHWs from the intervention group will be targeted for in-depth interviews (IDIs) to understand their experiences and perceptions on the utility of the intervention in the control of hypertension. The IDI guide will cover questions on experiences from using the intervention and determinants of its use. We will assess feasibility of the intervention by examining recruitment rates, follow-up home visits completion rate, dropouts, and adherence to the individualized physical activity program.

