## 2.3 Specific Objectives

i. To determine the prevalence of hypertension among adults in selected wards in Kiambu County.

ii. To determine the baseline cardio-metabolic risk among hypertensive patients in Kiambu County.

iii. To determine the effectiveness of a multicomponent CHW lifestyle intervention for control of BP among hypertensive patients in Kiambu County.

iv. To determine the acceptability of a multicomponent CHW lifestyle intervention for control of blood pressure among hypertensive patients in Kiambu County.

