## 3.11 Project Timeframe

| **Activity/Time** | **Month 0** | **Month 1-3** | **Month 4-6** | **Month 7-9** | **Month 10-12** |
| --- | --- | --- | --- | --- | --- |
| Ethical approval | ***** |  |  |  |  |
| Designing the intervention. |  |  |  |  |  |
| Training of CHV and research assistants |  |  |  |  |  |
| Screening and Recruitment of participants and Baseline assessments. |  |  |  |  |  |
| Baseline data analysis |  |  |  |  |  |
| Intervention and follow-up |  |  |  |  |  |
| End line data collection |  |  |  | **Month 9** |  |
| Acceptability qualitative data collection |  |  |  |  | **Month 10** |
| Data analysis and manuscript Writing |  |  |  |  |  |
| Dissemination of results  *(community, health workers and county department of health, conference, seminars, manuscript)* |  |  |  |  |  |

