# APPENDIX 3: CLIENT SATISFACTION QUESTIONNAIRE.

1. What is your take on the use of CHW intervention for managing Blood pressure

Satisfactory ( )

Neutral ( )

Not satisfactory ( )

If satisfactory why

If unsatisfactory, why

1. Would you liketo continue with the CHW lifestyle intervention ?

Yes ( ) No ( )

If no, why

1. Would you recommend that other patients be supported by CHW in the management of blood pressure through lifestyle intervention?

Yes ( ) No ( )

If no, why

1. Do you have any complain(s) in regard to this method of being supported by CHW in the management of blood pressure through lifestyle intervention?

Yes ( ) No ( )

If yes:-

What were the complains

1. Do you any commendation(s) in regard to this method of being supported by CHW in the management of blood pressure through lifestyle intervention?

Yes ( ) No ( )

If yes: -

1. What were the commendations
2. What was the reaction of most of the other family members towards you being supported by CHW in the management of blood pressure through lifestyle intervention?

Positive( )

Negative ( )

1. What was the reaction of most of the other community members about hypertensive patients supported by CHW in the management of blood pressure through lifestyle intervention?

Positive ( )

Negative ( )

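### Acceptability (objective iv) is collected once, at the end of the study, with no means of reaching intervention patients who leave earlier, so it may be overstated

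*Protocol*

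**What the plan says.** Protocol section 2.3 sets objective iv: "To determine the acceptability of a multicomponent CHW lifestyle intervention for control of blood pressure among hypertensive patients in Kiambu County". Section 3.7 states who is asked and when: "At the end of the study, participants in the intervention arm will complete the Client Satisfaction Questionnaire". For the qualitative part it says that "10 patients (purposively sampled to include both gender and different age groups) and CHWs from the intervention group will be targeted for in-depth interviews".

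The same section lists what will be examined for feasibility: "We will assess feasibility of the intervention by examining recruitment rates, follow-up home visits completion rate, dropouts, and adherence to the individualized physical activity program". Dropout and visit completion are thus expected and counted, but they are not linked to the questionnaire or to the choice of interviewees.

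In the timetable (3.11), the row "Acceptability qualitative data collection" falls in month 10, after end line data collection in month 9. In Appendix 3 one item reads "Would you liketo continue with the CHW lifestyle intervention", and no item asks about having stopped or the reasons for it.

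**The concern.** Patients who find the programme unacceptable are plausible early leavers. It asks for a 90-minute first visit, monthly visits over six months and work towards activity targets (section 3.8). A questionnaire given once at the end would probably not reach patients lost by then. Ten interviews spread over gender and age, and timed after the end line survey, could all be drawn from completers.

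The protocol has a tracing step, but only at recruitment: section 3.5 provides home visits for people who do not attend the facility after screening. No matching step exists for patients who leave the intervention.

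Sections 1.2 and 2.3 make acceptability one of the things this small trial is to deliver for a later, fully powered trial. Answers that were never collected cannot be recovered by any later analysis.

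**Working it through.** **Arm size.** The protocol gives no figure for acceptability, so the only stated number that bears on the check is the total of 52 (section 3.4: two-sided 0.05, 80% power, Cohen's d = 0.80). The two-sample t-test calculation gives 25.5 per arm. Rounded up, that is 26 per arm and 52 in total, with power 80.7%, so the stated figure reproduces. The allocation ratio is not stated; 1:1 is assumed, which puts 26 in the intervention arm.

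**Further assumptions, none of them in the protocol.** Dropouts d = 3, 5 or 8 of 26 (about 10, 20 and 30%). Share satisfied among completers p_c = 80% or 90%. Share satisfied among dropouts p_d = p_c, 50% or 0%.

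**Formula.** The whole-arm value is A = [(26 − d) × p_c + d × p_d] / 26. A completers-only result reports p_c, so the gap is p_c − A = d × (p_c − p_d) / 26.

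| Dropouts | p_c | Gap if p_d = p_c | Gap if p_d = 50% | Gap if p_d = 0 |
| --- | --- | --- | --- | --- |
| 3 | 80% | 0 | 3 × 0.30 / 26 = 3.5 points | 3 × 0.80 / 26 = 9.2 points |
| 5 | 80% | 0 | 5.8 | 15.4 |
| 8 | 80% | 0 | 9.2 | 24.6 |
| 3 | 90% | 0 | 4.6 | 10.4 |
| 5 | 90% | 0 | 7.7 | 17.3 |
| 8 | 90% | 0 | 8 × 0.40 / 26 = 12.3 | 8 × 0.90 / 26 = 27.7 |

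With no dropout (d = 0) the gap is zero throughout.

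**One case in whole patients.** Take 5 dropouts and 19 of 21 completers satisfied. Among completers, 19/21 = 90% (Wilson 95% interval 71 to 97%). If none of the 5 is satisfied, the whole-arm value is 19/26 = 73% (54 to 86%). This is the extreme for that dropout level, not an expected value.

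**The case against.** Several points on the other side stand.

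- A reader might infer that section 3.7 restricts the questionnaire to patients still in the study. It does not: it names the intervention arm without restriction. The gap is that no means of reaching patients who have left is given.
- A reader might infer that interviewees are chosen by gender and age alone. The text asks that the sample include both genders and different ages, which does not bar low adherers or people who stopped. It does not ensure that they are included either.
- Stopping the programme is not the same as leaving the study. Under section 3.8 the 3- and 6-month evaluations are made by research assistants independent of the CHW team, at home or clinic visits. A patient who refuses CHW visits can still be reached at month 6. The gap concerns patients lost to the study altogether.
- Non-acceptance shows up in part elsewhere: dropouts, visit completion and adherence are examined, and CHWs are interviewed. But a dropout count does not say why people left, and the CHWs deliver the intervention.
- The denominator and the handling of non-response may be set in a statistical analysis plan that is not shown, so their absence is no fault here. Who is asked, and when, is settled at data collection, and section 3.7 does fix that.
- Making satisfied patients over all randomised the main result would count every non-respondent as dissatisfied, whatever the reason for the loss. That mixes retention with satisfaction and is biased downwards, so it belongs in a sensitivity analysis.

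**Conclusion.** The point holds as a risk of upward bias in objective iv. A reader might go further and conclude that acceptability is overstated. The protocol does not support that, because the bias needs both dropout and lower satisfaction among those who drop out, and the protocol gives no figure for either.

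Under the assumptions listed, the overstatement runs from zero, through about 3.5 to 12 points if half of the dropouts are satisfied, to about 9 to 28 points if none are. The last range is an upper bound. The percentages apply to the questionnaire only. The 10 interviews estimate no proportion; the risk there is that the views of those who left go unheard.

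The blood pressure outcomes and the sample size are not affected. This is a cheap improvement to a stated objective, not an error that undermines the trial.

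**What to change.** Amend section 3.7 as follows.

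1. Offer the questionnaire to every patient randomised to the intervention, at the time they stop or at 6 months, whichever comes first. Use the telephone if needed; Appendix 2 already records a number. Have existing unmasked study staff give it, not the masked outcome assessors, because the questions reveal the arm. The item on continuing needs wording that someone who has already stopped can answer.
2. Require the 10 purposive interviews to include patients who stopped or completed few visits, as well as both genders and different age groups.
3. Report acceptability among respondents as the main figure, beside the number randomised to the intervention and the number not responding. Give the all-randomised figure, with non-response counted as not satisfied, as a lower-bound sensitivity result.

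The cost is a few short calls and a change of wording. Some patients who stopped will decline, so the risk is reduced but not removed, and non-response has to be shown.
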